### 8.3.2 Per Protocol Population

The Per Protocol Population (PP) will comprise only patients of the Full Analysis Population (only for maintenance phase) while excluding patients if any of the following criteria are met:

- Administration of less than two cycles of maintenance treatment if the reason for discontinuation was any other than death, progression of disease or continued unacceptable toxicities despite optimal treatment or dose reduction
- Any violation of major inclusion criteria or major exclusion criteria.
- Other major protocol violations such as wrong treatment received.
- Lack of any efficacy data after start of maintenance treatment.

Major violations will be determined independently of knowledge of response to therapy. A data review will be conducted prior to database lock based on all data to review protocol deviations, to discuss specific unforeseeable data issues and to allocate the subjects to the analysis sets. The associated decisions are documented and approved in the Data Review Meeting protocol. Protocol violations resulting in an exclusion from the Per Protocol Population will be described in the Clinical Study Report. All patients in the PP will be analyzed within their group of actual treatment received.

### 8.3.3 Safety Population

The Safety Population consists of all randomized patients who started maintenance treatment. All patients will be analyzed within their group of actual treatment received.

Furthermore, an additional induction therapy specific safety population will be defined to allow analyzing toxicity of induction therapy. All enrolled patients who started induction will be included.

Patients who cannot be included in any of the above mentioned analysis populations will be excluded from the statistical analyses for the respective population. Any recorded data of these patients will be listed in the appendix to the Clinical Study Report.

## **8.4 Methods of Statistical Analysis**

### **8.4.1 General Statistical Considerations**

The statistical evaluation will be carried out by ClinAssess GmbH. Statistical analysis is based on the International Conference on Harmonization (ICH) Guidelines “Structure and Content of Clinical Study Reports” and “Statistical Principles for Clinical Trials”.

Data will be analyzed using the SAS software package version 9.4 or higher on the Windows platform.

Study-specific SAS programs will be written for individual patient data listings and for aggregated analyses of adverse events and laboratory values. The biometrical analysis will be accompanied by the appropriate internal quality control according to ClinAssess’s current SOPs. The data analysis will be performed according to the statistical analysis plan (SAP) which will be finalised prior to database lock and prior to any statistical analysis. Any changes to the statistical analysis planned in the protocol are to be justified and documented in the SAP if they were decided before database lock. Any changes made to the SAP after the database lock will be documented in the clinical study report.

All data recorded in the case report forms describing the sample, the efficacy and the safety will be analyzed descriptively. Categorical data will be presented in contingency tables with frequencies and percentages. Continuous data will be summarized with at least the following: frequency (n), median, quartiles, mean, standard deviation (standard error), minimum and maximum. Number of patients with protocol deviations during the study and listings describing the deviations will be provided.

In general, chi-square tests will be used to compare percentages in a two-by-two contingency table, replaced by Fisher’s exact test if the expected frequency in at least one cell of the associated table is less than 5. Stratified two-by-two contingency tables will be analyzed using Cochran-Mantel-Haenszel tests. Comparison of ordinal variables between treatment arms will be performed using the asymptotic Wilcoxon-Mann-Whitney test, replaced by its exact version in case of ordinal categories with small number of categories and/or sparse data within categories. Any shift in location of quantitative variables between study groups will be performed with Wilcoxon-Mann-Whitney tests as well.

Time-to-event data will be analyzed by Kaplan-Meier methods, when merely non-informative censoring occurs. For statistical comparison, the logrank-test will be provided supplemented by multivariate Cox proportional hazards models.

The primary endpoint of this trial will be subjected to confirmatory statistical hypothesis testing applying the one-sided significance level of 10%. All other statistical tests are to be interpreted on an exploratory perspective. Consequently, no adjustment for multiple testing is foreseen.

Confirmatory statistical analysis of the primary efficacy parameter will be performed within the Full Analysis Population (Intent-to-Treat analysis). The Per Protocol Population merely serves for sensitivity analysis. All safety analyses will be performed within the Safety Population.

#### **8.4.2 Demographics and Baseline Characteristics**

All demographic and clinical characteristics recorded at baseline will be submitted to descriptive analyses using descriptive statistics by means of listing, tables and figures, if applicable. This analysis will be performed for all patients enrolled to the trial and subsequently for all patients randomized. The latter analysis will be stratified by treatment arms to assess homogeneity.

#### **8.4.3 Efficacy Evaluation**

##### *Efficacy of induction phase*

To describe the efficacy of induction phase all patients enrolled to the trial with documented start of induction therapy will be subjected to descriptive analysis.

- *Objective response after 12 weeks of induction chemotherapy*

Objective response after 12 weeks is defined as the objective response, i.e. CR or PR, measured at the tumor assessment 12 weeks after start of induction. Patients without any documented tumor assessment are considered to have experienced a progressive disease, in case of therapy discontinuation due to progressive disease or early death (defined as death prior to first scheduled tumor assessment after start of treatment). For statistical analysis, the distribution of best response categories will be provided based on all patients who have started induction phase.

- *Overall Survival*

For exploratory purposes, the overall survival experience between start of induction therapy and date of randomization will also be subjected to statistical analysis. This analysis will comprise all patients who have started induction phase.

##### *Primary efficacy parameter (Progression-free survival)*

The primary efficacy parameter of the trial is progression-free survival (PFS). PFS will be defined as the time length between the date of randomization and the date of first disease

progression (according to RECIST criteria V1.1, see appendix 4) or death (whichever occurs first).

Patients alive without first objective disease progression will be censored at the last time known to be alive and without known objective disease progression

First of all, the distribution of progression-free survival time will be described using Kaplan-Meier methods. These analyses will be presented by treatment arm and stratified by prognostic risk groups used at randomization. Estimates of median progression-free survival and estimates of progression-free survival rates for specific time points will be extracted from the Kaplan-Meier analyses together with the associated 80% confidence limits.

For confirmatory testing, the difference in progression-free survival between the two treatment arms according to the hypothesis system defined in section 8.1, a stratified logrank test will be applied. The stratification factors of response to induction therapy (CR/PR vs. SD), prior oxaliplatin-containing adjuvant therapy (yes vs. no) and planned dosage of maintenance therapy (full dosage of panitumumab vs. reduced dosage of panitumumab) will be applied. The one-sided significance level is predefined as 10%. Furthermore, stratified Cox regression model will be used to estimate the hazard ratio. For sensitivity analysis, a multivariate Cox proportional hazards model will also be fitted using the stratification factors at randomization as covariates in addition to the treatment parameter.

*Secondary efficacy parameter (Time from randomization until failure of treatment strategy)*

Time from randomization until failure of treatment strategy is defined as the time from randomisation to second objective disease progression, or death from any cause, whichever first. Patients alive and for whom a second objective disease progression has not been observed will be censored at the last time known to be alive and without known second objective disease progression. A sensitivity analysis for this efficacy parameter will be performed to account for those patients who do start re-induction therapy despite of lack of first objective progression and for patients who do not start re-induction despite of being alive and having a first objective progression during maintenance. These patients will be censored at the time of start of re-induction and the date of first objective progression, respectively.

The distribution of the time to failure of treatment strategy will be described using Kaplan-Meier methods. These analyses will be stratified by treatment arm and prognostic risk groups used for randomization. Estimates of median time to failure of treatment strategy and estimates of failure rates for specific time points will be extracted from the Kaplan-Meier analyses together with the associated 80% confidence limits.

The difference in time to failure of treatment strategy between the two treatment arms will be tested using a stratified logrank test as already described for progression-free survival above.

Furthermore, Cox proportional hazards models as already described for progression-free survival will be applied to yield adjusted estimates of the associated hazard ratios.

Secondary efficacy parameter (Progression-free survival of re-induction)

Progression-free survival of re-induction will be defined as the time length between the date of objective disease progression during maintenance and the date of first disease progression (according to RECIST criteria 1.1, see appendix 4) or death after start of re-induction (whichever occurs first). The Subgroup of patients with progression during/following maintenance and start of re-induction will be considered for this analysis. Patients alive with no documented progression during re-induction will be censored at the last documented visit without known progression of disease. Exploratory statistical analysis will consist of Kaplan-Meier analyses and Cox regression modelling.

Secondary efficacy parameter (Overall survival)

Overall survival will be defined as the time length between date of randomization and the date of death from any cause or the date of last follow-up in case of no documentation of death. All reported deaths occurring after randomization will be included, regardless whether they occur in maintenance, re-induction or following treatment discontinuation. Statistical analysis of overall survival will be conducted in analogy to the statistical analysis of the primary efficacy parameter.

Overall survival will also be analysed as the time length between date of registration (enrolment) and the date of death from any cause or the date of last follow-up in case of no documentation of death. All reported deaths occurring after registration/enrolment will be included, regardless whether they occur in induction, maintenance, re-induction or following treatment discontinuation. Statistical analysis of overall survival will be conducted in analogy to the statistical analysis of the primary efficacy parameter.

Secondary efficacy parameters (objective best response during maintenance and re-induction)

Best objective response within maintenance (comparison randomization image to assessments during maintenance) and re-induction phase (comparison of progression image during maintenance to images during re-induction phase) is defined as the best response documented within each specific therapy phase. Patients without any documented tumor assessment within the respective therapy phase are considered to have experienced a progressive disease, in case of therapy discontinuation due to progressive disease or early death (defined as death prior to first scheduled tumor assessment within each treatment phase). The distribution of best response categories within different treatment phases will be described.

For statistical comparison of treatment arms with respect to best response during maintenance and best response during re-induction, patients experiencing PR or CR will be considered as

responders. Point estimates of responder rates, the estimated difference in response rates and the associated 95% confidence intervals will be provided. The Cochran-Mantel-Haenszel chi-square test stratified by the same factors as for the analysis of progression-free survival will be used to compare treatment arms. An unadjusted Chi-square test result will also be provided.

Secondary parameter (Quality of Life)

Quality of life will be evaluated using the validated EORTC QLQ-C30, FACT-EGFRI 18, Skindex-16 and DLQI questionnaires. Data will be scored according to the algorithm described in the respective scoring manuals. For all quality of life domains and items, descriptive analyses will be presented stratified by visit and treatment arm.

Statistical comparison of quality of life between treatment arms may be distorted due to large quantities of missing questionnaires. Thus, the extent and process of missing data will be investigated. In case that data are missing completely at random, complete case analyses will be applied without biasing the results; otherwise treatment arms will be compared using longitudinal data modeling techniques.

For descriptive statistical analysis, summary tables will be provided showing measures of location and dispersion (minimum, quartiles, median, maximum, mean and standard deviation) stratified by visit and treatment arm. Furthermore, individual score items will be subjected to statistical analysis. Absolute changes of QoL-scores from baseline will be tabulated stratified by treatment group and visit. For graphical illustrations, Box-Whisker diagrams will be presented across visits for each treatment group.

For each domain, the proportion of patients in each arm with  $\geq 10$  points deterioration at each visit will be compared. It has been shown that this degree of change is perceptible and clinically significant on the 100 point scale. The numbers and percentages of patients with deterioration ( $\geq 10$  points deterioration), no change (less than 10 points deterioration/improvement) and improvements ( $\geq 10$  points improvement) will also be presented. Nonparametric (exact) Wilcoxon-Mann-Whitney tests will be applied for exploratory comparison purposes. In order to account for non-ignorable missing values due to death, progression or lost to follow-up, supplementary time profile analyses relative to baseline will be performed consisting of conditional descriptive analyses, given QoL-data up to a certain visit x, i.e. QoL tables at a specific visit x will be presented for patients with EOT-visit at or after visit x only.

In addition, time-to-deterioration-analyses will be conducted for assessing any long term differences between treatment arms. Patients will be considered to have deteriorated for a given domain if a deterioration of at least 10 points on the 100 point scale is observed after randomization. Patients without deterioration will be censored at the time of the last QoL assessment. Kaplan-Meier methods will be used for associated data descriptions. For

comparison purposes, logrank tests will be applied. Additional details of the QoL analysis will be described in the SAP.

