 The baseline tumor assessment must be done within 21 days prior to treatment start. Tumor assessment (CT or MRI) will be done according to RECIST 1.1 and will comprise thorax and abdomen. Radionuclide bone scan/skeletal x-ray for suspected bone metastases, and cranial CT for suspected CNS metastases will only be performed if clinically indicated. During the treatment phase tumor assessments will be performed 12 weeks after start of induction therapy and every 8 weeks during maintenance and re-induction therapy with a visit window of +/- 7 days. For patients discontinuing maintenance or re-induction prior to documentation of disease progression, disease assessment will continue every 8 weeks (+/- 7 days) until disease progression is documented or other anti-cancer therapy is started, whichever comes first

 To be evaluated according to NCI-CTCAE version 4.03

 Only patients with documented wild-type *RAS* (exon 2 [codons 12/13], exon 3 [codons 59/61], and exon 4 [codons 117/146] of KRAS **and** NRAS) may be included, resulting from primary or metastatic tumor (tested anytime).

 Optional: exploratory analyses will be performed on paraffin-embedded archived tumor tissue and circulating tumor cells/ tumor DNA. The following will be collected during screening:

- 1 Tumor block (paraffinated)
- 1 PAXGene DNA-Tube (8,5ml)
- 1 PAXGene RNA-Tube (8,5ml)
- 1 EDTA-Tube (7ml)
- 1 Serum-Tube (5ml)
- 1 Streck Tube (for cell free DNA analysis) (9ml)

 Quality of life will be assessed using the EORTC QLQ-C 30, DLQI, FACT-EGFRI 18 and Skindex-16 questionnaires

 Current symptoms and/ or residual toxicities from prior therapy; all adverse events from date of informed consent are to be documented

 ECG during treatment and for end of treatment visit only if clinically indicated

 The first visit of the long-term follow-up period will take place three months after the EOT visit. Follow-up for the individual patient will continue until death or until 2 years after randomization of the last randomized patient (whichever occurs first). Every effort will be made to collect the exact date of death.

 During Follow-up, tumor assessments will only be documented at 8 week intervals for patients who discontinued treatment before progression of disease occurred.

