The following are defined as non-target lesions: bone lesions, leptomeningeal disease, pleural/pericardial effusion, ascites, inflammatory breast disease, lymphangitis, cystic lesions and lesions not measurable by computed tomography (CT) or magnetic resonance imaging (MRI). All non-target lesions are described over time and need not be measured.

The tumor assessment for inclusion should be recorded and measured within 21 days prior to treatment start of cycle 1. If a cycle of any FOLFOX regimen has been administered before enrolment due to urgent treatment need and yet unconfirmed RAS status this baseline CT / MRI must be performed before start of that cycle and still within 21 days prior to start of cycle 1. Please take care to avoid any delays within that tight schedule.

Tumor assessments will be performed 12 weeks after treatment start with induction therapy and every 8 weeks during maintenance therapy and re-induction. During the maintenance and re-induction period, disease assessments will be performed every 8 weeks, independent of chemotherapy cycle delay.

Please note that for subjects discontinuing maintenance or re-induction therapy prior to documentation of disease progression, tumor assessments will be performed at 8 week intervals (+/- 7 days) until disease progression is documented.

In order to assess progression during maintenance therapy, tumor assessments during maintenance will be compared to the tumor assessment performed at randomization (i.e., tumor assessment in week 12 of the study). In order to assess progression during re-induction, the tumor assessment at the start of re-induction therapy will serve as a reference (i.e., that tumor assessment showing progression during maintenance (1st progression)).

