### **5.2.4 Follow-Up**

After discontinuation of treatment, all patients will be followed-up every 3 months. The first visit of the long-term follow-up period will take place 3 months after the EOT visit. Overall collection of long-term follow-up data will terminate 2 years after randomization of the last subject. The following information will be collected during the follow-up visits:

- Physical examination
- Body weight
- ECOG performance status
- Survival data
- Subsequent anti-cancer therapy
- Adverse events continuing from treatment phase will be followed-up until the event has resolved or stabilized.

For subjects discontinuing maintenance or re-induction therapy prior to documentation of disease progression, tumor assessments will be performed at 8 week intervals (+/- 7 days) until disease progression is documented.

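### Primary PFS censoring is not tied to a tumour assessment, and the protocol contradicts itself on when scans stop, so follow-up without imaging can count as progression-free time

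*Protocol*

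**What the plan says.** **Endpoint and censoring.** Protocol 8.4.3 (primary efficacy parameter) defines PFS from randomisation to first progression by RECIST 1.1 or death. For everyone else: "Patients alive without first objective disease progression will be censored at the last time known to be alive and without known objective disease progression". This is the only censoring rule given for the primary endpoint. It mentions neither the last tumour assessment nor missed scans nor new therapy.

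**When scans stop.** Footnote 9 of the flow chart, on patients who leave maintenance or re-induction before progression: "disease assessment will continue every 8 weeks (+/- 7 days) until disease progression is documented or other anti-cancer therapy is started, whichever comes first". Section 5.1.1, on the same patients: "tumor assessments will be performed at 8 week intervals (+/- 7 days) until disease progression is documented". Section 5.2.4 repeats the rule of 5.1.1, and section 3.1.4 also continues 8-weekly scans until progression is shown on CT or MRI. None of these three sections stops scans at new therapy.

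**Contacts without scans.** Section 5.2.4: "After discontinuation of treatment, all patients will be followed-up every 3 months". The items listed for those visits are physical examination, weight, ECOG status, survival, subsequent therapy and ongoing adverse events. Imaging is required separately, for patients who stopped before progression. Footnote 16 continues follow-up until death or 2 years after the last randomisation.

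**Neighbouring endpoint.** For PFS of re-induction, 8.4.3 uses different wording: such patients "will be censored at the last documented visit without known progression of disease". That is also not tied to a scan.

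**The concern.** Progression is established by imaging. A patient who is no longer scanned cannot have a progression recorded, yet at each contact remains alive and without known progression. Under the literal rule the censoring date keeps moving forward through time in which the event could not be observed. If the patient later dies, the death is a PFS event at the date of death, however long after the last scan.

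Both effects replace an unobserved progression time by a longer time that depends mainly on survival. Medians are lengthened. If the same share of each arm is affected, the hazard ratio is pulled towards 1. If the shares differ, the test can be biased either way. The trial is open-label, so unequal departure from imaging is possible. PFS is the only endpoint tested confirmatorily (8.4.1), so the definition matters.

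**Working it through.** **1. The plan's own figure.** Inputs from section 8.2: HR 0.75, one-sided alpha 10%, power 80%, 1:1 allocation. The Schoenfeld formula gives

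d = 4 (z₀.₉₀ + z₀.₈₀)² / (ln HR)² = 4 (1.2816 + 0.8416)² / (0.2877)² ≈ 218.

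This matches the stated 218 events. The sample size arithmetic is sound, and the issue lies in the endpoint rule.

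**2. Which patients are exposed.**

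| Rule followed | Unscanned time that can count as progression-free |
|---|---|
| 3.1.4, 5.1.1, 5.2.4: scan to progression | About one 8-week interval, plus any missed scans |
| Footnote 9: stop at new anti-cancer therapy | From the last scan to death or the end of follow-up |

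The protocol does not say which prevails.

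**3. Illustration at trial size.** From the documents: exponential PFS with medians of 10 and 7.5 months, 252 patients, one-sided 10% log-rank test. Assumed, not in the documents:
- a share of each arm stops scans at a random point before progression but stays in survival follow-up;
- median survival after that point is 20 months;
- randomisation is spread over months 3-87, with the data cut at month 93.

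Results with 10% per arm leaving imaging:

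| Rule | HR | Power |
|---|---|---|
| Complete imaging | 0.75 | 80% |
| Plan, literal reading | about 0.79 | 65-69% across three simulations |
| Living patients censored at last scan, later deaths still events | 0.77 | 74% |
| All who stop censored at last scan, later deaths not counted | 0.74 | 79% |

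Under the literal reading the medians come out at about 11.0 and 8.4 months instead of 10 and 7.5. About 69% of those who stop scans die before the data cut. The censoring sentence does not apply to them, since it covers only patients who are alive. So changing the date recovers 74 − 69 = 5 of the 80 − 69 = 11 points lost, or about half. With 3% per arm leaving imaging, power under the plan is about 77%.

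**4. Cross-check with a different stopping model.** Here 400,000 patients per arm are scanned every 8 weeks, stopping is independent of progression, and the data cut falls 24-108 months after randomisation. Power at 218 events is Φ(½√218 × |ln HR| − 1.2816), with ½√218 = 7.382.
- HR 0.75: 7.382 × 0.2877 − 1.2816 = 0.842, power 80%.
- 10% stop per arm, median survival 12 months afterwards, HR 0.786: 7.382 × 0.2408 − 1.2816 = 0.496, power 69%.
- The same with 20 months, HR 0.805: 7.382 × 0.2169 − 1.2816 = 0.320, power about 62-63%.

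With every such patient censored at the last scan, the HR stays at 0.746-0.754 for equal stopping of 5-20% per arm.

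**5. Unequal stopping.** In the model of step 4, 10% in arm A and 20% in arm B gives an HR of 0.83-0.90; 20% in A and 10% in B gives 0.76-0.77. The direction depends on which arm leaves imaging more often.

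**The case against.** **The wording is not explicitly a last-contact rule.** It requires the patient to be known alive and also without known progression, and for overall survival the authors write of the date of last follow-up instead. An analyst could take the sentence to mean the last assessment. This stands in part: the text is ambiguous. Absence of known progression is nevertheless satisfied at any contact with none on record, so the literal reading is the longer one.

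**Long unscanned time is not the planned course.** Three sections require 8-weekly scans to progression, footnote 17 provides for 8-weekly assessments during follow-up, and patients who enter re-induction early are still scanned. This stands. A long tail needs footnote 9 to prevail together with new therapy before progression, or else missed scans.

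**Much of the simulated loss comes from late deaths, not from the censoring date.** This stands and shapes the fix.

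**Detailed missed-assessment rules often sit in the SAP.** That is fair, and their absence is not the point. The censoring rule and the two scan-stop rules are stated in the protocol itself.

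**Stronger readings to avoid.** A reader might infer a gravely inflated type I error. A stress case with 15% stopping in arm A, 5% in arm B and no true effect does give one-sided false positives of about 38-44% against 10%, and about 1% with the arms reversed. Neither the rates nor the imbalance is in the documents, and stopping there is informative by construction: even censoring at the last scan leaves 18-20%. A reader might also infer that section 5.1.1, by taking the week-12 scan as the reference for maintenance, departs from how RECIST 1.1 reads progression. Appendix 4 gives only a citation and a file that is not shown, and 5.1.1 can be read as naming the baseline for each phase. The documents do not support that point.

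**Conclusion.** The concern holds in moderate form and should be fixed. Primary PFS lacks a link between censoring and imaging, and one footnote contradicts three sections on when imaging ends. The size of the effect cannot be fixed from the documents. It ranges from little, if scans run to progression and few are missed, to an HR of about 0.79 and power of about 65-69% if 10% per arm leave imaging early. These figures rest on the assumed stopping shares and on 20 months' median survival after stopping. With unequal stopping the bias could go either way, but nothing in the protocol shows that it will occur. The 218 events and 80% power are correct as calculated.

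**What to change.** **(a) Section 8.4.3.** Censor primary PFS at the last evaluable tumour assessment without progression, or at randomisation if there is none. In the same place, state how deaths and progressions after missed or stopped assessments are handled; the new date alone recovers only about half of the loss. Align the wording for time to failure of strategy and for PFS of re-induction.

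**(b) Scan schedule.** Reconcile footnote 9 with sections 3.1.4, 5.1.1 and 5.2.4 so that one scan-stop rule applies. Which rule is for the sponsor to decide; the censoring rule in (a) can be applied under either.

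**Cost.** Text changes only, to be made before database lock. The censoring change needs no new data, and the event target does not change. Reported medians may be slightly shorter, and a few late events may be censored, depending on the rule chosen for them.
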